## 2. Methods

### 2.1. Design and Participants

The design (Figure 1) is a two-branch random controlled design with participants who will receive the intervention protocol assigned to the intervention group and those who will receive the usual care assigned to the control group. The intervention will begin between 4–6 weeks after the initial evaluation. Usual care consists of attending pregnancy follow-up and monitoring appointments, resolving any questions that may arise during the process with the midwives, and attending group prenatal preparation classes. Participants will be assessed before and after, and one, three and six months after finishing the intervention. The trial is registered on ClinicalTrials.gov (accessed on 20 September 2024). The registration ID is NCT06609291.

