### 2.7. Sample Size

Power calculations were conducted to determine the minimum sample size. As there was no research describing the efficacy of CBT delivered via videoconference in this population, power calculations were based on published RCTs of unguided CBT for antenatal depression [38]. To detect a between-group effect corresponding to Cohen’s d of 0.55, the minimum sample size for each group (α = 0.05, 80% power) was 53 participants. Therefore, we aimed to recruit a minimum sample of 140 participants to allow for expected attrition.

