### 2.8. Analysis Plan

The primary analysis will compare the mean scores of EDS-3A, STAI-E and GAD-7 between the two groups before and after the intervention and one month, 3 months and 6 months after the end of the intervention to evaluate the effectiveness of the protocol in preventing anxiety symptoms. Similar analyses will be performed for the secondary result on depressive symptomatology. For the GAD, the frequencies in the two groups will be compared at the same evaluation periods.

Regarding the effectiveness of treatment, descriptive statistics will be calculated for all questionnaires. Variance analyses for repeated measurements will be performed to compare the differences between each initial score obtained with the different administered questionnaires and the scores at T1 (end of treatment), T2 (after 1 month), T3 (after 3 months) and T4 (after 6 months) will be evaluated. Bonferroni post hoc comparisons will also be conducted. The number of evaluations compared will need to be taken into account to adjust the *p*-value in the Bonferroni test with the aim of minimizing type 1 errors. The treatment effect will be calculated using Cohen’s d for each of the follow-up times. The Reliable Change Index will be calculated for each time in order to determine any significant clinical changes occurring in each individual case post-treatment. To compare differences in GAD, the chi-square test and Fisher’s exact test will be used in the contrast of 2 × 2 tables. In addition, Cochran’s Q test will be used to determine the existence of differences across time points and McNemar’s test will be used to compare the differences in categorical variables between time points in a paired manner.

Data will be analyzed using the Statistical Package for Social Science (SPSS) for Windows version 23.0.

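### Section 2.8 does not adjust the arm comparison for the t0 score, so scores already collected before randomisation are used inefficiently on either reading of the plan

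*Protocol article*

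**What the plan says.** Section 2.8 describes the comparison in two ways. Its first paragraph calls primary a comparison of the two groups' mean EDS-3A, STAI-E and GAD-7 scores before the intervention, after it, and at the three follow-ups. This matches the primary outcome in 2.3.1. Its second paragraph, on treatment effectiveness, plans repeated-measures ANOVA to "compare the differences between each initial score obtained with the different administered questionnaires and the scores at T1 (end of treatment", and likewise T2, T3 and T4. Bonferroni comparisons and Cohen's d at each follow-up time come after that. The EPDS is to be analysed similarly. Neither paragraph names the t0 score as a covariate.

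Section 2.7 sizes the trial as follows: "To detect a between-group effect corresponding to Cohen’s d of 0.55", "the minimum sample size for each group (α = 0.05, 80% power) was 53 participants". It adds that "we aimed to recruit a minimum sample of 140 participants to allow for expected attrition". No correlation between initial and later scores appears there or elsewhere. Section 2.2 sets 2:1 allocation after the baseline questionnaire, and 2.1 says that "The intervention will begin between 4–6 weeks after the initial evaluation".

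**The concern.** Every randomised woman has a t0 score on each scale. How that score enters the arm comparison decides whether it removes noise or adds it. Subtracting it in full is right only if follow-up tracks baseline one for one. If the correlation is modest, subtraction brings in baseline variation unrelated to the follow-up score. Ignoring it leaves explainable variation in the error term.

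A modest correlation is conceivable here. The initial score is taken at 16 weeks' gestation or earlier and the intervention starts 4 to 6 weeks later. The seventh weekly session falls 6 weeks after the first, so t1 is about 10 to 12 weeks after t0. Six more months (about 26 weeks) put t4 at about 36 to 38 weeks after t0. One instrument is a state scale and another has three items. These features suggest that ρ may fall over time, but they do not give its value.

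Precision, and possibly power, is at stake. So is the handling of chance imbalance: with change scores, an arm that happens to start more anxious will tend to appear to improve more.

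**Working it through.** **Inputs.** From 2.7: d = 0.55, α = 0.05, 80% power, 53 per group (106 evaluable), 140 recruited. From 2.2: 2:1 allocation. Assumed, because the protocol does not state them: ρ, equal SDs at t0 and follow-up, and d in raw-score SD units.

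**The plan's figure.** A two-sided two-sample t-test at d = 0.55 (noncentral t) has power 79.3% with 52 per group and 80.1% with 53. The stated 53 is therefore reproduced by an unadjusted two-group comparison, with no correlation in it. A one-sided test would need about 41.

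**Variance of the arm contrast at one visit**, relative to a raw follow-up comparison:
- raw follow-up score: 1
- change from t0: 1 + 1 − 2ρ = 2(1−ρ)
- follow-up adjusted for t0: 1−ρ²

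Adjusted over change is (1−ρ²)/[2(1−ρ)] = (1+ρ)/2, so change loses (1−ρ)/2. Adjusted over raw is 1−ρ², so raw loses ρ².

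**Power at 53 per group.** The standardised effect is 0.55/√(2(1−ρ)) for change and 0.55/√(1−ρ²) for adjusted. The one degree of freedom spent on the covariate is ignored.

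| ρ | loss, change vs adjusted | loss, raw vs adjusted | power, change | power, raw | power, adjusted |
|---|---|---|---|---|---|
| 0.2 | 40% | 4% | 60.2% | 80.1% | 81.7% |
| 0.3 | 35% | 9% | 65.9% | 80.1% | 83.7% |
| 0.4 | 30% | 16% | 72.6% | 80.1% | 86.4% |
| 0.5 | 25% | 25% | 80.1% | 80.1% | 90.0% |
| 0.6 | 20% | 36% | 88.0% | 80.1% | 93.9% |
| 0.8 | 10% | 64% | 99.3% | 80.1% | 99.7% |

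The losses are in variance (sample-size equivalent). For ρ from 0.6 down to 0.3, the standard error of a change contrast is 12% to 24% larger than that of the adjusted one.

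**Where a change contrast reaches 80%.** At 53:53, it needs 2(1−ρ) ≤ 1, so ρ ≥ 0.5. For other splits, compare n₁n₂/(n₁+n₂) with 53×53/106 = 26.5:
- 106 evaluable at 2:1 (71:35): 71×35/106 = 23.4. Then 2(1−ρ) ≤ 23.4/26.5 = 0.88, so ρ is at least about 0.56.
- all 140 retained at 2:1 (93:47): 93×47/140 = 31.2. Then 2(1−ρ) ≤ 31.2/26.5 = 1.18, so ρ is at least about 0.41.

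**Chance imbalance.** Suppose the arms differ by Δ at t0 by chance. Given Δ, the change contrast is off by −(1−ρ)Δ, the raw follow-up contrast by +ρΔ, and the adjusted contrast by zero on average. At ρ = 0.5, the first two each carry half the imbalance, in opposite directions.

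**The case against.** The strongest objection is that the plan is ambiguous. A reader might infer from the second paragraph of 2.8 that effectiveness is tested only on change from baseline. The documents do not support that: the analysis labelled primary compares group means, 2.3.1 defines the outcome the same way, and the ANOVA sentence names no group term. Nor is every arm contrast from a repeated-measures ANOVA a change-score difference. The group main effect is not, and a five-visit interaction does not reduce to a single change score. Even among change contrasts the threshold moves. With equal correlations and a constant effect, the mean of T1 to T4 minus t0 has variance 1.25(1−ρ), which reaches 80% power at ρ = 0.2. This objection stands, and it limits the power claim.

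Second, 2.7 does not say which SD standardises d. If 0.55 is in change-score SD units, the same 53 per group results and a change analysis has its 80% at any ρ. This also stands.

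Third, under randomisation, change-score and raw comparisons are unbiased on average. The imbalance point holds only conditionally on the imbalance that occurs. That is correct, and makes this a matter of efficiency rather than validity.

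Fourth, a condensed article may leave covariates to a fuller plan. That carries less weight, because 2.8 states a concrete method. The point concerns that method, not a missing detail.

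None of these objections reaches the remedy. On the change reading and on the raw-mean reading alike, adjustment is never less precise, apart from one degree of freedom.

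**Conclusion.** The point holds as a free improvement. Section 2.8 makes no use of the t0 score as a covariate, and both ways it describes the comparison are less precise than the adjusted one for any ρ strictly between 0 and 1, given equal SDs. For an assumed ρ of 0.3 to 0.6, a single-visit change contrast loses 35% to 20% of variance efficiency; the loss is 10% at ρ = 0.8. With d = 0.55 in raw-score SD units and 53 per group, its power is 66% to 88%, against 84% to 94% adjusted.

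A reader might infer that the trial falls short of its stated 80% power, or that the 20% to 35% loss is established. Neither follows. The protocol gives no ρ, and the break-even of 0.5 applies to one contrast at 53:53. It is about 0.56 with 106 evaluable at 2:1 and about 0.41 if all 140 are retained. A shortfall is possible but not shown.

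**What to change.** In 2.8, define the treatment effect on EDS-3A, STAI-E, GAD-7 and EPDS at each of T1 to T4 as the arm difference in follow-up score adjusted for the t0 score of the same scale, with a 95% CI. Use ANCOVA at each visit, or a mixed model for T1 to T4 with the t0 score as a covariate. Report change from the initial score descriptively only.

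The cost is one or two sentences. The t0 scores are collected before randomisation under 2.2, so no visit, questionnaire or participant is added. The sample size in 2.7 can stay as it is, and the gain is extra precision.

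### Cheap improvement, not an error: Holm's step-down could replace plain Bonferroni in section 2.8 under the same family-wise error limit, gaining about 7–11 points of power per visit if d = 0.55 persists and less otherwise

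*Protocol article*

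**What the plan says.** Section 2.8 first sets out the between-group comparison: "The primary analysis will compare the mean scores of EDS-3A, STAI-E and GAD-7 between the two groups before and after the intervention", and again at 1, 3 and 6 months. A separate paragraph then describes the modelling: "Variance analyses for repeated measurements will be performed to compare the differences between each initial score obtained with the different administered questionnaires", set against the scores at T1 to T4. Directly after that comes "Bonferroni post hoc comparisons will also be conducted", and then "The number of evaluations compared will need to be taken into account" when the p-value is adjusted, with control of type 1 error as the stated aim. No step-down procedure is named. The number of comparisons is not given, and the text does not say whether the Bonferroni tests are arm comparisons at each visit or time contrasts.

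Section 2.7 supplies the only effect size, "To detect a between-group effect corresponding to Cohen’s d of 0.55", and the resulting size: "the minimum sample size for each group (α = 0.05, 80% power) was 53 participants". That effect is not tied to a visit. Section 2.2 randomises 2:1.

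**The concern.** Plain Bonferroni compares every p-value with alpha divided by the full family size, however strong the evidence at the other visits. Holm relaxes the threshold after each rejection. For a family of four it tests the ordered p-values at 0.05/4 = 0.0125, 0.05/3 = 0.0167, 0.05/2 = 0.025 and 0.05, and stops at the first failure. The first step is the Bonferroni test, so Holm cannot reject less. Its family-wise guarantee needs no assumption about correlation, which suits repeated scores on the same women.

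The trial is small, and it intends to report a treatment effect at each follow-up. If the benefit lasts, the single-step adjustment makes it harder than necessary to show at which visits it is present.

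**Working it through.** **Inputs.** From 2.7: d = 0.55, alpha 0.05, 80% power, 53 per group. From 2.8: four follow-ups, T1–T4. From 2.2: 2:1 allocation, so 2 × 53 = 106 analysed women split about 71:35. Assumed, because the article gives none: the family is the four arm comparisons within one scale (m = 4), the visit test statistics share a correlation r, tests are two-sided, and d at each visit follows one of the patterns below.

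**The plan's own figure.** n per group = 2(1.960 + 0.842)²/0.55² = 51.9, so 52 by the normal formula. The t-based calculation gives 52.87, so 53. The stated figure reproduces with two-sided alpha 0.05 and no adjustment.

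**Bonferroni at m = 4.** The expected test statistic is d·√(n₁n₂/(n₁+n₂)).

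- 53:53: 0.55 × √26.5 = 2.831. Power is Φ(2.831 − 1.960) = 80.8% unadjusted and Φ(2.831 − 2.498) = 63.1% at alpha 0.0125.
- 71:35: 0.55 × √(71 × 35/106) = 2.663. Power is 75.9% unadjusted and 56.6% at alpha 0.0125.

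**Holm.** Its power depends on r, so it was simulated with 300,000 draws of four equally correlated normal statistics per case.

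| Case, d = 0.55 at all four visits | Bonferroni, per visit | Holm, per visit | All four visits, Bonferroni / Holm | At least one visit, both methods |
|---|---|---|---|---|
| 53:53, r = 0.5 | 63% | 72% | 33% / 54% | 89% |
| 53:53, r = 0.6 | 63% | 72% | 36% / 57% | 86% |
| 71:35, r = 0.5 | 57% | 66% | 26% / 46% | 85% |
| 71:35, r = 0.6 | 57% | 65% | 29% / 49% | 82% |

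At 53:53 the gain per visit runs from 10.8 points at r = 0 to 6.7 points at r = 0.9.

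**Other effect patterns** (53:53, m = 4):

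- Fading 0.55/0.40/0.30/0.20: gains of 1.5/4.5/5.7/5.2 points at r = 0.5 and 1.2/4.5/5.9/5.9 at r = 0.6. The chance of all four visits at r = 0.6 is 4% and 10%.
- d = 0.30 throughout: 3.3 points at r = 0.5 and 3.6 at r = 0.6.
- d = 0.55 at three visits only: 4–6 points at those visits. At two visits only: about 2. At one visit only: about 0.

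**Other families.** If the Bonferroni tests are the ten within-group contrasts among five time points (assumed change of 0.55 SD, then flat, n = 53), the gain is 1.6 points at r = 0.5 (88.4% to 90.0%) and 0.2 at r = 0.7 (99.1% to 99.3%). If the family were all twelve scale-by-visit arm comparisons, it would be 11.0 points at r = 0.5 and d = 0.55 throughout (48.7% to 59.7%).

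**Error rate.** With no effect anywhere, the simulated family-wise error is the same for both methods: 4.9% at r = 0, 4.3% at r = 0.5 and 4.0% at r = 0.6. With d = 0.55 at three visits and none at the fourth, the false rejection rate at the fourth is 1.3% for Bonferroni and 3.3% for Holm at r = 0.5. Holm uses more of the 5% allowance but stays within it.

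**The case against.** The strongest reply is that nothing here is wrong. Section 2.8 wants type 1 error limited, and Bonferroni does that. Preferring another valid procedure is a matter of efficiency. That stands, and the point is put only as an improvement to a choice the article states.

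The second reply concerns size. A reader might infer that the trial gives up a flat 9 points at every visit, with each p-value tested at 0.0125. The article supports neither. It gives no family size, and the Bonferroni sentence follows a description of baseline-to-follow-up comparisons, so time contrasts are a fair reading; under that reading almost nothing is gained. The d of 0.55 comes from trials of unguided CBT for antenatal depression, whereas section 3.1 describes a universal programme for women at any level of risk. A constant 0.55 out to 6 months is therefore the favourable case.

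Third, the stake is limited. The primary objective in the Introduction is anxiety during pregnancy, no passage requires significance at all four visits, and the chance of at least one significant visit is identical. This stands too.

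Fourth, Holm has no simple matching simultaneous intervals, and Cohen's d at each follow-up is a planned output. This is a genuine but small cost. None of these replies removes the central fact that Holm never rejects fewer hypotheses under the same error limit.

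**Conclusion.** The point holds as an optional, low-cost improvement. That Holm is at least as powerful needs no assumption; the size of the gain does. With m = 4 arm comparisons within a scale and d = 0.55 at every visit, it is about 7–11 points per visit over r = 0 to 0.9. It shrinks to the smaller values shown above when the effect fades, is weaker throughout or is confined to one visit, or when the tests are within-group. Effect pattern and family matter more than the correlation.

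Two further inferences should be resisted. Holm would not restore the 80% power of section 2.7: at 53 per group it reaches about 72%, because that calculation used unadjusted alpha for one comparison. Nor does Holm within each scale deal with multiplicity across the three anxiety scales.

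**What to change.** In section 2.8, replace the Bonferroni sentence with wording such as: *Between-arm comparisons at T1, T2, T3 and T4 will be adjusted within each scale by the Holm step-down procedure (family of four, two-sided family-wise alpha 0.05). Holm-adjusted p-values will be reported beside the estimated differences with 95% confidence intervals labelled as unadjusted.* This also settles what the family is.

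The cost is one sentence and simple arithmetic on the unadjusted p-values, with no extra women or data. An unadjusted interval may exclude zero where the Holm-adjusted p-value is not significant, so the label on the intervals is needed. The change should be made before any outcome data are seen by arm.

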## 1. Introduction

Anxiety is one of the most frequent disorders during the perinatal stage. Its prevalence is between 15% and 23% [1,2,3,4] during the pregnancy and between 3.7% and 15.0% [1,5] during postpartum. In Spain, the prevalence of anxiety ranges from 16.8 to 19.5% throughout pregnancy [3]. Additionally, one in ten women will experience comorbid anxiety and depression during pregnancy and one in twelve during the postpartum period [6]. The disparity in prevalence may be due to the moment of evaluation, the use of different evaluation instruments and cut-off points and cultural differences in relation to the importance given to mental health in a specific country and/or culture. Although its prevalence is high, research on treating anxiety during this period is recent [7,8].

Perinatal anxiety is associated with adverse health effects in women and their babies. Regarding mothers, it has been associated with an increased probability of developing postpartum depression [9], a higher risk of preeclampsia, obstetric complications and bonding problems [10,11,12]. As for newborns, they have been found to be more likely to have lower birth weight and poor cognitive development, among others [13,14], hence the importance of detecting and intervening early in prenatal anxiety to promote the well-being of mothers and children, because despite the negative consequences associated with perinatal anxiety, the majority of women are not identified or treated [7,15], as less than 15% receive treatment [16]. Given the high prevalence of prenatal anxiety and the potential for adverse consequences, early treatment is recommended [17,18]. Evidence on the effectiveness of psychological interventions during pregnancy is scarce [17,18,19,20], highlighting the importance of having specific interventions.

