### 2.3. Outcomes and Allocation of Participants to Trial Groups

#### 2.3.1. Primary Outcome

The primary outcome measure will be the difference in the mean anxiety scores between the intervention and control groups assessed by the EDS-3A, STAI and GAD-7 questionnaire before and at the end of the intervention, and one month, 3 months and 6 months after the intervention. Generalized anxiety disorder (GAD) will also be evaluated through the DSM-5 clinical interview at the same time points. In this case, the percentages found will be compared.

The Edinburgh Depression Scale-Anxiety Subscale (EDS-3A) is the anxiety subscale of the Edinburgh Postnatal Depression Scale (EPDS) [42]. Different studies, e.g., [43,44] have found that three items (3, 4, 5) can detect anxiety in women during the perinatal period. Each of the three items has four response options (0 = none, 1 = somewhat, 2 = quite a bit, and 3 = a lot). The total score of the subscale ranges from 0 to 9. The cut-off point used in the EDS-3A to detect anxious symptomatology will be ≥5 [45].

The State–Trait Anxiety Inventory (STAI) [46] assesses both the current level of anxiety and the individual’s predisposition to suffering from anxiety. It consists of 40 items, 20 of which refer to the state subscale (STAI-E), with the other 20 referring to the trait subscale (STAI-R). The score for each subscale ranges from 0 to 60, with higher scores indicating higher levels of anxiety. In this case, the State Anxiety Subscale (STAI-E) will be applied; the recommended cut-off point for women is greater than 31 (75th percentile).

Generalized Anxiety Disorder Screener (GAD-7) [47] is a self-administered instrument consisting of seven items with four response options. The total score ranges from 0 to 21, with the highest scores being the most severe. The GAD-7 has been validated for use in Spanish-speaking pregnant women [48]. The cut-off point used to detect anxiety symptoms will be ≥7 [49].

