## 3. Intervention

### 3.1. Rationale

The intervention was based on the principles of cognitive–behavioral therapy (CBT) and transdiagnostic treatments for emotional problems and includes three sections that address the main components of CBT: thoughts, pleasant activities and social contacts. CBT is one of the interventions that has obtained the best results for the treatment and prevention of perinatal anxiety [7,52,53]. On the other hand, transdiagnostic interventions may be more beneficial than specific interventions for each disorder, as scientific evidence suggests [7,37]. The need to develop this perinatal anxiety prevention program aimed at pregnant women is justified by the high prevalence of anxiety in the perinatal stage, as well as its possible consequences for both the mother and the baby [8,54]. Furthermore, there is a high comorbidity between symptoms of perinatal depression and anxiety [6], which indicates the importance of having a transdiagnostic intervention. Another aspect that highlights the need for a program of this type is the scarcity of existing psychological interventions to treat anxiety during pregnancy and postpartum [8,55]. A prevention program has been chosen because it would allow anxiety to be treated before it becomes a problem for the mother and her baby and would prevent future suffering [26]. Specifically, it would be a universal prevention program intended for all pregnant women regardless of whether or not they are at risk of anxiety. These programs have the advantage of increasing awareness about perinatal mental health as they provide information about its prevalence and risk factors, as well as tools to cope with emotional distress and increase the support network.

A CBT prevention program has been selected for development because it is found to obtain some of the best results in clinical practice [7,24]. The techniques included in the program, such as cognitive restructuring, behavioral activation or social support, have been selected because they repeatedly appear in the reviewed interventions that have shown greater effectiveness [7,8,24,32]. It should be noted that the intervention will not exclusively address anxiety, but also depression, due to the high comorbidity they present [6].

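### Section 2.8 uses the Reliable Change Index alone to determine clinical change; it shows only change beyond measurement error and should be paired with the protocol's own cut-offs (minor)

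*Protocol article*

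**What the plan says.** Section 2.8 gives the RCI its task in one sentence: "The Reliable Change Index will be calculated for each time in order to determine any significant clinical changes occurring in each individual case post-treatment". It attaches no criterion of clinical status to the index.

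Section 2.3 supplies such criteria. For the EDS-3A, "The total score of the subscale ranges from 0 to 9" and "The cut-off point used in the EDS-3A to detect anxious symptomatology will be ≥5". For the STAI-E, "the recommended cut-off point for women is greater than 31 (75th percentile"). For the GAD-7, "The cut-off point used to detect anxiety symptoms will be ≥7". Section 2.3.2 gives 10 for the EPDS.

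The population is unselected for symptoms. Section 3.1 says "it would be a universal prevention program intended for all pregnant women regardless of whether or not they are at risk of anxiety", and Section 2.4 sets no symptom threshold for entry. On how many women may be symptomatic, the Introduction says "In Spain, the prevalence of anxiety ranges from 16.8 to 19.5% throughout pregnancy".

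The RCI is not the main analysis. Section 2.8 says "The primary analysis will compare the mean scores of EDS-3A, STAI-E and GAD-7 between the two groups before and after the intervention", with the later follow-ups added, and compares frequencies of interview-diagnosed generalized anxiety disorder between the arms. The hypothesis in the Abstract concerns how many women have anxious symptoms.

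**The concern.** The RCI divides a change score by the standard error of a difference between two measurements. A large value means that the change is unlikely to be measurement noise. It says nothing about which side of a clinical threshold the woman started or finished on. Section 2.8 nevertheless asks it to identify clinical change, and so gives the statistic a conclusion that it cannot carry alone.

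A universal sample sharpens this. Most women should start below the cut-offs. Some of them can fall by more than measurement error without ever having been symptomatic by the protocol's definition. Others start too near zero to improve reliably at all. A woman with a very high score can improve reliably and still be symptomatic.

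At stake is the meaning of any published rate of clinically significant change. A reader would take it as the share of women whose status changed. Beyond the RCI, Section 2.8 names no individual-level analysis of the scales, while the stated hypothesis is about how many women are symptomatic.

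**Working it through.** **The plan's own figure.** The only design figure is 53 per group for d = 0.55, α = 0.05 and 80% power. A two-sided t-test calculation gives 52.87, hence 53. It reproduces and has no bearing on this point. No RCI figure is stated.

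**Inputs from the document.** Cut-offs: EDS-3A ≥5 (scale 0–9), STAI-E >31 (0–60), GAD-7 ≥7 (0–21). Prevalence of anxiety in pregnancy in Spain, 16.8–19.5%, serves as a proxy for the share at or above a cut-off at baseline.

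**Assumed inputs.** SDs, reliabilities *r* and distribution shapes are not in the document, so ranges are shown.

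**Step 1: smallest reliable change.** Threshold = 1.96 × SD × √(2(1 − r)), rounded up to whole points. Example for the GAD-7 with SD 4 and r = 0.8: 1.96 × 4 × √0.4 = 4.96, so 5 points. The table uses r = 0.7–0.9.

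| Scale | Assumed SD | Smallest reliable drop | Lowest baseline that allows a reliable drop ending at or above the cut-off | Baselines below the cut-off that allow a reliable drop |
|---|---|---|---|---|
| EDS-3A | 1.5–2.5 | 2–4 | 7–9 | 2–4, narrowing to 4 only |
| STAI-E | 8–12 | 8–19 | 40–51 | 8–31, narrowing to 19–31 |
| GAD-7 | 3–5 | 3–8 | 10–15 | 3–6, narrowing to none |

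The fourth column is the lowest symptomatic score plus the drop, for example 7 + 3 = 10. So a reliable improver can remain symptomatic on every scale, but only from a high start. A woman who was never symptomatic can be a reliable improver on the EDS-3A and STAI-E throughout the range. On the GAD-7 this needs a drop of 6 points or fewer, which holds in six of the nine combinations of SD and reliability.

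**Step 2: how common a high start is.** Take the EDS-3A as roughly normal with SD 2.1 and 16.8–19.5% at ≥5 (continuity-corrected). With r = 0.6, 0.7 and 0.8 the thresholds are 3.68, 3.19 and 2.60, so 4, 4 and 3 points. To improve reliably and stay at ≥5, a woman must start at 8 (3-point drop) or 9 (4-point drop).
- Share at 8 or more: 0.8–1.1%. Share at 9: 0.2–0.3%. Among 140 women: 140 × 0.011 = 1.5 at most.
- GAD-7, same shape, SD 4: 2.5–3.2% at ≥11 and 1.4–1.7% at ≥12. Among 140 women: 140 × 0.014 = 2.0 to 140 × 0.032 = 4.5.

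These are the women for whom the error is possible, not those in whom it occurs. A skewed distribution would raise the shares.

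**Step 3: floor.** In the same EDS-3A model, 46–50% score ≤2 and 65–69% score ≤3. They cannot drop by 3 or 4 points respectively.

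**Step 4: simulation with a skewed score.** A GAD-7-like score was drawn from a gamma distribution (shape 1.5), with a correlation of 0.6 between occasions, 16.8% or 19.5% at ≥7 at baseline, r = 0.8 or 0.9, and an improvement of 0, 0.3 or 0.55 SD. Across the 12 settings, of all reliable improvers:
- 44–78% crossed from ≥7 to below 7;
- 8–51% had started below 7;
- 5–17% were still at ≥7.

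Hence 22–56% (100 − 78 to 100 − 44) did not change status by the protocol's cut-off. Starting below was the commoner of the two errors in 10 of the 12 settings; the exceptions were two settings with 19.5% prevalence and r = 0.8. Of all women, 39–65% scored too low to improve reliably.

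**Step 5: deterioration.** In the same simulation reliable deterioration fell from 6.7–16.6% with no shift to 1.5–5.0% with a 0.55 SD shift. New scores at ≥7 fell from about 9–10% to about 3%. The index therefore does carry information on prevention if worsening is counted by arm.

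**The case against.** The strongest reply is that this is one supplementary sentence in a condensed article. Section 2.8 rests the question of prevention on group means and on the frequency of interview-diagnosed disorder. It also plans Cochran's Q and McNemar's tests for categorical variables, which could be applied to cut-off status. How the RCI is put into practice may be settled in a fuller plan. Every size above depends on assumed SDs, reliabilities and shapes.

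Much of this stands, and it sets the weight of the point. Choosing the SD and reliability can indeed be left to the analysis plan. What does not fall away is the sentence itself: it states a purpose that the RCI alone cannot serve.

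A reader might go further and infer three things that the document does not support.
- *That the RCI will routinely label still-symptomatic women as clinically changed.* It can, but only from a high baseline, which few women in a universal sample will have (Step 2).
- *That the RCI cannot show prevention.* The document does not give it that role. Its wording covers any change, is not limited to improvement or to one arm, and the index is signed, so reliable worsening can be compared between arms.
- *That the results would be wrong in both directions because women kept well count as unchanged.* For a woman whose score did not move, that classification is correct.

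It is also fair to say that requiring a cut-off crossing does not cure the floor effect, since it further narrows who can register improvement. The floor is better met by following women who start below the cut-off for new symptoms.

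**Conclusion.** The point holds as a minor one. Section 2.8 equates reliable change with clinical change and leaves the protocol's own cut-offs unused at that step. Applied as written, the rule can label as clinically changed some women who were never above a cut-off and, usually less often, some who remain above it. The illustrative size is 22–56% of reliable improvers without a change of status, with 39–65% of all women too low at baseline to improve reliably. Those figures rest on the assumed gamma shape, correlation and reliabilities, and on prevalence as a proxy for baseline cut-off status. The conceptual point needs none of these assumptions. No primary or secondary outcome comparison depends on the sentence.

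**What to change.** In Section 2.8:

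1. Report the RCI as reliable change, giving improvement and deterioration separately in both arms at each time.
2. Call a change clinically significant only when it is reliable and also crosses the protocol's cut-off: EDS-3A ≥5, STAI-E >31, GAD-7 ≥7, and the stated 10 for the EPDS.
3. Among women below the cut-off at t0, compare new scores above the cut-off, and reliable deterioration, between arms at each time with a risk difference and 95% confidence interval. Label this a supplementary analysis that matches the stated hypothesis on the frequency of anxious symptoms.

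The cost is a change of wording and a few lines of analysis on data already collected; enrolment, assessments and the intervention are untouched. The downside is that, with about 140 women, several scales and four post-baseline times, some categories will be small and their intervals wide. The results should be read as descriptive support for the main comparison.
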